**Study protocol**

1. Study Type.

1.1. Single-center, three-year cross-sectional study in patients with rheumatoid arthritis (RA), systemic lupus erythematosus (SLE), and controls to estimate the relationships between serum expression and gene signature of type I, II, and III interferons (and subtypes) and carotid intima-media thickness, plaque presence, and carotid stiffness in patients with RA, SLE, and controls. Additionally, this study will assess the relationship between alterations in serum and gene expression with other cardiovascular disease determinants such as lipid profile, insulin resistance, beta cell dysfunction, reverse cholesterol transport, etc.

1.2. A six-month prospective study in a subgroup of RA patients initiating anti-TNF therapies. Eligible patients starting anti-TNF therapy will be studied before and after six months of treatment. We will determine if the modifications in IFN molecule levels and expression change after treatment and if changes also occur in lipid profile and insulin resistance associated with potential changes in IFN. Ultrasound techniques will not be performed during this second visit on these patients.

1.3. Variables.

1.3.1. Primary outcome variable (dependent): carotid artery intima-media thickness and plaque presence, carotid stiffness measurement (endothelial dysfunction); reverse cholesterol transport; insulin resistance and beta cell dysfunction.

1.3.2. Secondary variables: explanatory (independent) variables: serum concentrations and gene expression of IFN types I, II, and III and subtypes. Other dependent variables: a) abnormal lipid profile including paraoxonase/arylesterase and myeloperoxidase antioxidant activity, cholesterol ester transfer protein activity, lecithin-cholesterol acyltransferase, reverse cholesterol transport measurements, PCSK9 (Proprotein Convertase Subtilisin/Kexin Type 9) levels; b) insulin resistance indices and beta cell function (measured via serum insulin and C-peptide and calculated using HOMA2 – homeostatic model assessment). Confounding variables: sex, age, body mass index, obesity, blood pressure, antihypertensive treatment, fasting glucose, presence of diabetes, smoking, statin use.

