Demographic data, surgical history, smoking, vascular comorbidities, and current treatment will be recorded. Weight and height will be measured to determine body mass index (BMI) (body weight divided by height squared in kg/m2) and waist-to-hip ratio. Disease activity will be assessed using DAS28 (Disease Activity Score 28 Joints), CDAI (Clinical Disease Activity Index), or SDAI (Simple Disease Activity Index), and HAQ (Health Assessment Questionnaire). Metabolic syndrome will be defined following the 2005 National Cholesterol Education Program Adult Treatment Panel III (ATP III) criteria. Cardiovascular risk in the Spanish population will be assessed via the SCORE2 (Systematic Coronary Risk Evaluation version 2 updated). Disease activity and damage in SLE will be evaluated through the Systemic Lupus Erythematosus Disease Activity Index (SLEDAI-2K) and the SLICC/ACR damage index (SDI), respectively. Disease severity will also be assessed by the Katz index.

2. Population Selection

2.1. Inclusion Criteria: 1. Men or women not pregnant or breastfeeding; 2. ≥18 years and <70 years old; 3. Patients under any disease-modifying drug treatment (including those already receiving biologicals) or initiating biological treatment (anti-TNF or others); 4. If receiving oral corticosteroids, dose must be ≤ 10 mg prednisone and stable for at least one month prior to inclusion; 5. Patients capable and willing to sign informed consent.

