2.2. Exclusion Criteria: Patients with any of the following will be ineligible: 1. Autoimmune rheumatic diseases other than RA or SLE, such as mixed connective tissue disease, scleroderma, polymyositis, or systemic involvement secondary to RA (e.g., vasculitis, pulmonary fibrosis, or Felty’s syndrome). Sjögren’s syndrome with RA or SLE is not an exclusion criterion; 2. Functional Class IV RA as defined by the ACR Functional Status Classification (complete or substantial disability confining the patient to bed or wheelchair with inability for self-care). 3. History or current presence of inflammatory joint disease other than RA (e.g., gout, reactive arthritis, psoriatic arthritis, seronegative spondyloarthropathy, Lyme disease). 4. Glomerular filtration rate under 60 ml/min/1.73 m2 and presence of active renal disease. 5. Pregnant or lactating women. 6. Evidence of uncontrolled severe concomitant cardiovascular, nervous system, pulmonary (including COPD), renal, hepatic, endocrine (including diabetes mellitus), or gastrointestinal diseases, or any which, in the investigator’s judgment, would alter the interferon system profile. 7. Body weight >150 kg or BMI >50 kg/m2. 8. History of alcoholism, drug addiction or substance abuse within six months prior to screening visit.

3.. Data Collection

3.1. Baseline. Data for each patient will be recorded in a Case Report Form (CRF) in paper and electronic formats. CRF data must be verifiable against source documents such as clinical histories, laboratory data, and ultrasound reports. Concentrations obtained by the different assays will be attached to each patient’s CRF with standard curves and validation criteria. The data will be included in an electronic database facilitating statistical analysis. Blood samples will be collected fasting from the antecubital vein during patient and control study visits.

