5. Data Analysis Objectives. IFN gene expression scores are typically categorized (low, medium, high), but we will explore continuous and categorical IFN score analysis. Initially, multivariable analyses will compare IFN expression between patients with RA and SLE and controls. The relationship between IFN expression and carotid plaque presence, intima-media thickness, or arterial stiffness will be evaluated using multivariable linear or logistic regression. Differences in IFN effects on atheromatosis or carotid stiffness between diseases or between groups and controls will be assessed by adding interaction terms to regression models to determine if relationships differ among the three populations (RA, SLE, controls). A predictive model will be developed for interferon system molecules that, parsimoniously combined, predict carotid plaque presence or endothelial dysfunction. The relationship between IFN and other cardiovascular risk factors will be studied by multivariable linear/logistic regression. Stata 17 will be used for analysis; statistical significance is defined as a two-sided p-value <0.05.

6. Ethics. The project will be submitted to the Ethics Committee of our center. No patient or control will experience any change in care from the Rheumatology Department. Patients and controls will sign informed consent and will receive a study information sheet outlining objectives and interventions. The processing, communication, and transfer of all participants’ personal data are detailed in this application.

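### One RA-oriented eligibility list serves three groups: on its natural reading controls go unscreened, and exclusion 3 taken literally bars SLE patients with lupus arthritis

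*Protocol*

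**What the plan says.** Section 1.1 of the Protocol describes a "Single-center, three-year cross-sectional study in patients with rheumatoid arthritis (RA), systemic lupus erythematosus (SLE), and controls". Section 2 is the only text on population selection, and it does not mention controls.

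- **Inclusion 3 (Section 2.1)** asks for "Patients under any disease-modifying drug treatment (including those already receiving biologicals) or initiating biological treatment (anti-TNF or others".
- **The exclusion list (Section 2.2)** opens with "Patients with any of the following will be ineligible".
- **Exclusion 1** covers "Autoimmune rheumatic diseases other than RA or SLE", so it spares both study diseases.
- **Exclusion 3** covers "History or current presence of inflammatory joint disease other than RA", so it spares RA only. Its examples are gout and four other separate diagnoses. Lupus arthritis is not named either way.
- **Exclusions 4 to 8** deal with renal function, pregnancy and lactation, uncontrolled severe disease or anything judged to disturb the interferon profile, extreme body size, and substance misuse.

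Where the protocol means both populations, it says so. Section 6 states: "Patients and controls will sign informed consent". Sections 3.1 and 3.2 also name the two separately.

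**The concern.** Section 5 compares IFN expression in RA and SLE with that in controls. It then adds interaction terms to ask whether the link between IFN and carotid outcomes differs across the three populations. Both analyses need the groups to be selected by comparable rules, apart from the disease itself.

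Two features of Section 2 put that at risk. First, patients are screened for conditions that affect vessels or the interferon system, while nothing applies the same screen to controls or keeps RA, SLE or another autoimmune disease out of the control group. Second, the two exclusions that touch rheumatic and joint disease disagree on SLE. If exclusion 3 is applied as worded, the SLE group is selected on a manifestation of SLE. If recruiters differ in how they read it, the composition of that group depends on who recruits. Eligibility belongs in the protocol, so a SAP that is not shown could not supply it.

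**Working it through.** The document states no group sizes, prevalences or effect sizes for this point, so there is no planned figure to reproduce. The check is mainly textual.

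**Step 1. Whom does the list bind?** There are two readings, and they are alternatives.

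| | The word patients means patients only | The list binds every participant |
|---|---|---|
| Inclusion 3 | Does not concern controls | An untreated control fails it |
| Age limits, exclusions 4 to 8 | Not applied to controls | Applied to controls |
| Must controls be free of RA and SLE? | No rule | Still no rule, because exclusion 1 spares both |

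The protocol separates patients from controls elsewhere, so the left column is the natural reading. Neither column gives a workable definition of a control.

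**Step 2. Does the analysis repair this?** The confounders in Section 1.3.2 are age and sex, adiposity, blood pressure and its treatment, glucose and diabetes, smoking, and statins. Set against exclusions 4, 6 and 8, the list omits glomerular filtration rate, hepatic and pulmonary disease, established cardiovascular disease, substance misuse, and conditions that alter the interferon profile. The last matters most, because IFN is the main explanatory variable. Adjustment for the listed variables covers part of the differential screening, not all of it.

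**Step 3. Exclusions 1 and 3 side by side.** Exclusion 1 exempts RA and SLE; exclusion 3 exempts RA alone. Exclusion 3 also reaches back to past disease, and its examples are introduced as examples, so they do not close the list. Literally, an SLE patient with current or past lupus arthritis passes exclusion 1 and fails exclusion 3. If exclusion 3 means only separate joint diagnoses, the same patient passes both.

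**Step 4. How far could the SLE mean move?** Let f be the share of SLE patients removed by exclusion 3, and d the difference in mean between removed and remaining patients, in SD units. The full-group mean equals the remaining mean plus f × d, so the shift is f × d. Neither input is in the document. Taking f from 0.2 to 0.6 and d from 0.2 to 0.5 SD as pure assumptions:

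- smallest: 0.2 × 0.2 = 0.04 SD
- largest: 0.6 × 0.5 = 0.30 SD
- exclusion 3 read as separate diagnoses only: f = 0, shift = 0

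The sign of d is unknown, so the direction is too. The same expression would apply to controls, with f as the share carrying an unscreened condition, and the document gives no value there either.

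**The case against.** The best defence has four parts.

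**Exclusion 3 was probably not meant to catch lupus arthritis.** All its examples are separate diseases, and exclusion 1 admits SLE expressly. This stands as a statement of likely intent. It does not remove the inconsistency in wording, which leaves each recruiter to decide.

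**The analysis is multivariable, with age and sex among the confounders.** This stands too, and it disposes of any demand that controls be matched to patients. Choosing adjustment over matching is not an error. It does not answer the omitted conditions in Step 2.

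**Exclusion 6 concerns uncontrolled severe disease.** Patients with controlled disease are admitted, so the difference in screening is narrower than it may look. That is right, but exclusion 6 also covers any disease thought to alter the interferon profile, and that part is not narrow.

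**No bias has been shown.** Correct, and the point is put here only as a risk.

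A reader might also infer three stronger things that the document does not support:

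- That the list both leaves controls without exclusions and shuts them out through inclusion 3. These need opposite readings of the word patients, so they cannot both hold.
- That losing SLE patients with arthritis flattens the IFN slope. A narrower IFN range costs precision, but under a correctly specified linear model it does not by itself bias the slope. Nor does the document say that these patients differ in IFN.
- That the patient-versus-control difference in plaque prevalence is diluted by some calculable amount. Section 5 plans no such comparison, and the document gives no prevalences.

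**Conclusion.** The point holds as a defect in the eligibility rules and a risk of differential selection. On the natural reading of Section 2, the age limits and the renal, severe-disease and interferon-altering exclusions apply to patients and not to controls. On either reading, no rule keeps RA or SLE out of the control group. Separately, exclusions 1 and 3 are inconsistent on SLE, and the literal wording of exclusion 3 bars patients with past or present lupus arthritis.

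The analyses exposed are the RA/SLE-versus-control IFN comparison and the IFN-by-group interactions. Neither the size nor the direction of any bias can be established from the document. The 0.04 to 0.30 SD range for the SLE mean rests wholly on assumed inputs, and it becomes zero if exclusion 3 is applied narrowly. The case for changing the text rests on the wording being cheap to correct, whereas enrolment under unequal rules cannot readily be undone.

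**What to change.** Four changes to Section 2:

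1. Limit inclusion 3 and inclusion 4 to patients with RA or SLE.
2. State that the age limits and exclusions 4 to 8 apply equally to controls.
3. Require controls to have no RA, SLE, other autoimmune rheumatic disease or inflammatory joint disease.
4. Reconcile exclusion 3 with exclusion 1 by exempting joint involvement due to SLE itself.

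No matching is needed for this point. The cost is protocol wording and a slightly smaller pool of eligible controls.
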